### Objectives

The trial objectives are to:

• assess feasibility in terms of rates of participant recruitment and retention

• assess fidelity to the intervention

• conduct a qualitative assessment of feasibility from the perspective of multiple stakeholders

• conduct a preliminary evaluation of supported implementation compared with implementation alone

• investigate patient-related factors affecting patient outcome

• investigate stroke service-level factors potentially affecting stroke service outcomes to estimate the amount of unexplained variability in outcomes between Trusts and between patients

• confirm the choice of primary and secondary outcome measures for a full-scale cluster-randomised trial to evaluate effectiveness

• develop and test data collection tools for an economic evaluation within a full-scale cluster-randomised trial

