### Outcomes

#### Effectiveness

The primary effectiveness outcome will be incontinence (presence; absence). Measures will be taken at 6 weeks, 3 months and, for those recruited during the first three months, 12 months post stroke. The primary analysis will be of the 6-week data as conservative interventions for continence typically last six weeks [11,15], and an effect is most likely to be seen at this time point.

Secondary effectiveness outcomes will be: quality of life, frequency and severity of incontinence, urinary symptoms, activities of daily living (ADLs), and death; at 6 weeks, 3 months and, for those recruited during the first three months, 12 months post stroke.

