#### Ascertainment of outcomes

Presence/absence of incontinence will be measured by the International Consultation on Incontinence Questionnaire (ICIQ-UI Short Form) [51]. Absence of incontinence will be defined as the response 'never' to Question 3, 'How often do you leak urine?'; presence of incontinence will be defined as any other response to Question 3 (ranging from 'about once a week or less often' to 'all the time'). The ICIQ-UI Short Form has received a grading of A^new ^- highly recommended from the International Consultation on Incontinence Symptoms and Quality of Life Committee indicating published reports of acceptable reliability, validity and responsiveness in at least one study [52]. To our knowledge, the ICIQ-UI Short Form has not been used in the post-stroke population. We have conducted preliminary validation of the tool with six stroke survivors from our Patient, Public and Carer Involvement Group using the approach recommended by the ICIQ developers ([name], personal communication); all thought the tool was appropriate for use post-stroke and few problems were identified.

Quality of life will be measured using the Incontinence Quality of Life Instrument (I-QOL) [53,54] and the EuroQol (EQ-5D) [55]. Frequency and severity of incontinence will be ascertained using the Incontinence Severity Index [56]. Urinary symptoms will be measured using the Leicester Urinary Symptom questionnaire [57] and activities of daily living via the Barthel Index [58].

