In addition, the following baseline information about the patient will be recorded following consent: date of birth (age to be calculated*); sex; ethnicity; date of admission; date of stroke onset; date baseline questionnaire completed; location when recruited into the study; consciousness level (defined as either 'alert' or 'drowsy' on the 'Clinical Status on Admission' item of the European Stroke Database); side of body affected by stroke; type of stroke; location of stroke (OCSP classification[59]); co-morbidities (Charlson Comorbidity Index[60]; day seven Barthel Index [58]; pre-stroke Modified Rankin Scale [61]*; pre-stroke living circumstances*; Leicester Urinary Symptom questionnaire [57]; type of UI (urge UI, mixed UI, 'functional' UI or unclear); cognitive ability (6 Item Cognitive Impairment Test [62]); fluid intake; bowel function; relevant clinical investigations (e.g. mid stream urine, bladder scan); medications; living circumstances; verbal sub-section of the Glasgow Coma Scale [63]*; ability to lift both arms off the bed*; ability to walk independently*; ICIQ-UI Short Form [51]; Incontinence Severity Index [56]; EuroQol (EQ-5D) [55].

The six factors highlighted with a * above from the Edinburgh stroke case mix adjuster [64] will be collected to enhance patient-level adjustment for prognosis.

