### Economic evaluation

In this pilot trial, we will develop data collection tools to record resource use which will be used in a future, definitive trial. Tools will include: proformas for staff to record training and time spent on the intervention; a structured staff-observation schedule to allow independent assessment of time spent on the intervention; proforma to record resources (e.g. tests and investigations, length of stay) used in hospital (data will be obtained from the hospital information system); postal questionnaire about health and social service input, for self-completion by patients and carers. The postal questionnaires will be based on a design used previously by the applicants when querying input after discharge in a cohort of stroke patients.

Two measures will be used for the cost-utility analysis. The EuroQol (EQ-5D)[55], a generic quality of life measure, will be used to facilitate comparison with other studies and will allow us to estimate the benefit of the intervention in terms of quality adjusted life years (QALYs) gained. However, it has been suggested that the EQ-5D has a large ceiling effect and poor responsiveness in a non-stroke sample of women with urinary incontinence [68]. We will therefore also use a condition-specific measure, the Incontinence-Specific Quality of Life instrument (I-QOL, [52,53]), which has been shown to be the best continence-specific measure for use in clinical trials in terms of reliability, validity and responsiveness to change [67].

We will build on the cost-utility analysis by conducting an additional sensitivity analysis. We will review published economic evaluations that have estimated Quality Adjusted Life Years (QALYs) and extract the utility (quality-of-life) values they used. We will tabulate the basis for these figures in terms of the size of sample, which patients were questioned, what technique was used (EQ-5D or other), and how values were derived. We will use the data which seem to have the most validity in the sensitivity analysis.

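### I-QOL is the only outcome questionnaire missing from the itemised baseline list, so change from entry and adjustment for its own baseline are not available for it

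*Protocol article*

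**What the plan says.** Under Outcomes, Effectiveness, the article lists the secondary outcomes: "Secondary effectiveness outcomes will be: quality of life, frequency and severity of incontinence, urinary symptoms, activities of daily living (ADLs), and death". They are assessed at 6 weeks, 3 months and, for early recruits, 12 months.

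Under Ascertainment of outcomes it assigns the instruments. For the outcome at issue here: "Quality of life will be measured using the Incontinence Quality of Life Instrument (I-QOL) [53,54] and the EuroQol (EQ-5D) [55". Four other instruments cover the rest: the ICIQ-UI Short Form gives the primary outcome, the Incontinence Severity Index gives frequency and severity, the Leicester questionnaire gives symptoms, and the Barthel Index gives daily activities.

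The same section then itemises what is recorded at baseline. The list includes a day-seven Barthel Index and the Leicester questionnaire, and closes with "ICIQ-UI Short Form [51]; Incontinence Severity Index [56]; EuroQol (EQ-5D) [55". I-QOL is not in it, and no other section provides for I-QOL at entry.

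Under Economic evaluation, I-QOL joins EQ-5D as the second cost-utility measure and is described as the "best continence-specific measure for use in clinical trials in terms of reliability, validity and responsiveness to change". One of the Objectives is to "confirm the choice of primary and secondary outcome measures for a full-scale cluster-randomised trial to evaluate effectiveness".

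Under Data analysis, Outcomes, baseline values of the outcome variables are to enter the mixed models as covariates where that is appropriate, along with stroke classification, type of incontinence and the case-mix factors. Missing continuous outcomes are to be multiply imputed.

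**The concern.** Every other outcome questionnaire has a value at entry; I-QOL does not. Three things follow.

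- **Change from entry.** The article expects an effect to be most visible at six weeks. Over the interval from entry to six weeks, change can be computed for EQ-5D but not for I-QOL.
- **Imbalance.** There are four services per arm, and under Allocation concealment the staff who identify and recruit patients know their service's allocation. The Patient recruitment process section itself foresees selection by severity. For I-QOL, an imbalance at entry can be neither seen nor adjusted for directly.
- **Missing data.** A participant lost before six weeks has no I-QOL value at all, so imputation has to rest wholly on other variables. For EQ-5D an entry value is available if the baseline form was completed.

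At stake is the precision and robustness of one secondary outcome, and what the pilot can say about that instrument when it confirms the choice of measures.

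**Working it through.** **Step 1. Compare the two lists (both in Ascertainment of outcomes).**

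| Outcome questionnaire | In baseline list |
|---|---|
| ICIQ-UI Short Form | yes |
| I-QOL | **no** |
| EQ-5D | yes |
| Incontinence Severity Index | yes |
| Leicester Urinary Symptom questionnaire | yes |
| Barthel Index | yes (day seven) |

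Five of six are present; only I-QOL is missing. The list is introduced as additional information, but that does not bring I-QOL in, because the other five are all named again.

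**Step 2. What remains computable.** I-QOL is measured at 6 weeks, 3 months and, for early recruits, 12 months. Change between those points is available, and so is the difference between arms at each. Change from entry is not.

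**Step 3. Patient-level gain from an own baseline.** The article gives no correlation r between baseline and follow-up I-QOL, so r is assumed. Taking I-QOL as a continuous score, adjustment leaves 1 − r² of the patient-level variance:

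- r = 0.3: 1 − 0.09 = 0.91, a 9% reduction
- r = 0.6: 1 − 0.36 = 0.64, a 36% reduction

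The comparison is with no adjustment at all.

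**Step 4. Carry this to the service level.** Services are the randomised units. The Sample Size section expects 780 patients in 12 services, so 780/12 = 65 per service. With total variance set to 1, the variance of a service mean is ICC + (1 − ICC)/65. The ICC for I-QOL is not given; 0.05 and 0.01 are assumed.

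- ICC 0.05: 0.05 + 0.95/65 = 0.0500 + 0.0146 = 0.0646. The patient-level share is 0.0146/0.0646 = 0.226. Reductions of 9% and 36% in that share lower the total by 0.226 × 9% = 2.0% and 0.226 × 36% = 8.1%.
- ICC 0.01: 0.01 + 0.99/65 = 0.0100 + 0.0152 = 0.0252. The patient-level share is 0.0152/0.0252 = 0.604. The total falls by 0.604 × 9% = 5.4% and 0.604 × 36% = 21.7%.

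These figures assume that 65 patients per service contribute an I-QOL value, and they count no reduction in between-service variance. Fewer respondents would raise the patient-level share. Baseline measures that correlate with I-QOL would already recover an unknown part of the gain.

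**The case against.** The strongest reply is that this is a choice and not an error. Entry is in the acute phase and takes in drowsy, catheterised and consultee-consented patients, who already face a long baseline battery. A quality-of-life questionnaire about living with incontinence may make little sense so soon after stroke. An article need not justify each omission, and the substitute covariate can be left to the analysis plan. The baseline list is also loosely written (its types of incontinence leave out stress, which the inclusion criteria admit), so absence from it is not proof that the baseline form lacks I-QOL.

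Much of this stands. A deliberate omission is plausible, and because baseline covariates are planned only where appropriate, the analysis text is not contradicted. Recruitment and severity are monitored by cluster, which covers part of the imbalance risk. A baseline I-QOL would itself be self-reported after open allocation. Against that, four self-report questionnaires (Leicester, ICIQ-UI Short Form, Incontinence Severity Index and EQ-5D) are already in the same baseline set for the same patients, and the article gives no reason for treating I-QOL differently.

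A reader might also infer three stronger points that the document does not support:

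- *The trial cannot study change or responsiveness in I-QOL at all.* Only change from entry is lost.
- *The economic evaluation carries both measures in order to compare their responsiveness, or prefers I-QOL to EQ-5D.* It adds I-QOL alongside EQ-5D because outside evidence suggests EQ-5D responds poorly in women with incontinence who have not had a stroke. It plans no head-to-head comparison. The objective on outcome measures does not name responsiveness as its criterion; completion, missingness, distribution and differences at follow-up can all still inform it.
- *The I-QOL model has no baseline adjustment.* It has the case-mix factors, stroke classification and type of incontinence, and other baseline continence scores are collected. Only the instrument's own baseline is missing.

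**Conclusion.** The point holds in a limited form. On the article's own lists, I-QOL is the one outcome questionnaire of six without a baseline, so change from entry and own-baseline adjustment are unavailable for it. The comparison of arms at follow-up stays valid. The cost is a modest loss of precision and of protection against imbalance from unconcealed recruitment: about 2% to 8% of the variance of a service mean at ICC 0.05, or 5% to 22% at ICC 0.01. Those ranges rest on an assumed correlation of 0.3 to 0.6, assumed ICCs and 65 patients per service. They overstate the net loss to the extent that other baseline measures stand in. This is a worthwhile refinement for one secondary outcome in a pilot whose sample size was set pragmatically. It is not a flaw that threatens the trial's conclusions.

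**What to change.** 1. **In the analysis, in any case.** Include a baseline continence measure already collected (the Incontinence Severity Index or the ICIQ-UI Short Form), and baseline EQ-5D if wanted, as covariates in the I-QOL model and as predictors in its multiple imputation. This costs only wording.
2. **In data collection, where feasible.** Add I-QOL to the existing baseline visit in every arm for participants able to complete it, and use it as the baseline covariate for the I-QOL outcome. The cost is one more self-report questionnaire, added burden in the acute phase, and missing baseline values in patients with aphasia or cognitive impairment.
3. **If I-QOL is not added.** State that the pilot will not be used to judge the responsiveness of I-QOL from entry when it confirms the outcome measures for the full-scale trial. This too costs only wording.

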#### Data collection

Baseline data will be collected on entry to the trial by the research nurse. Outcome data will be collected at six weeks, three months and (for participants recruited within the first three months of the trial) twelve months post-stroke via postal questionnaires (or hand-delivered questionnaires if participants are still in hospital at six weeks). All participants with aphasia will be offered a face-to-face interview with the research nurse to collect outcome data; this will be conducted using appropriate communication aids (e.g. pictorial cards with a 'thumbs up' picture indicating 'yes' and a 'thumbs down' card indicating 'no'). Specialist help will be available from Speech and Language Therapists and Speakeasy, a specialist aphasia charity based in Ramsbottom, Bury (http://www.buryspeakeasy.org.uk/), if this is needed.

Postal and telephone reminders will be used if questionnaires are not returned within two weeks. Where completion of postal questionnaires is not possible, participants (or carers if a proxy is needed) will be invited to complete assessments over the telephone. If neither postal or telephone completion is possible, a face-to-face assessment in the participant's home will be offered.

We will collect intervention fidelity data for all participants in the active intervention groups during three (for sites with a nine month intervention period) or four (for sites with a 12 month intervention period) randomly selected weeks during each three-month period in which the stroke service is recruiting participants into the trial.

#### Blinding

It is not possible for the health professionals or patients to be blinded to the intervention. However, data collectors will be blinded. The trial statistician will not be blinded during the analysis, however the statistical analysis plan will be finalised prior to any outcome data being available to the trial statistician.

### Qualitative evaluation of implementation

An integrated qualitative evaluation will be conducted in order to describe implementation and assist in explaining why the intervention and its components were or were not successful. Semi-structured interviews will be conducted with patients at discharge and will seek patients' experiences of their treatment for incontinence and their views of the effectiveness of treatment.

We will use maximum variance sampling [65] to generate a range of participants (around 15-20 from each trial arm, but with the numbers determined by data saturation) in terms of gender, age, ethnicity, type of incontinence and stroke severity. Patients will also be chosen to reflect those with a range of outcomes at discharge (defined in terms of the frequency of incontinent episodes).

Qualitative, semi-structured interviews will be performed with health professionals (n = 15-20 per intervention group, but with the numbers determined by data saturation) involved in the intervention to explore experiences of implementing the intervention and drivers and barriers to successful implementation. Qualitative interviews (n = 15-20) will also be held with health professionals in the 'usual care' trial arm to facilitate comparison in terms of continence management across trial arms.

### Sample Size

The sample size is chosen pragmatically, rather than on the basis of a formal power calculation; our aim is to balance practicalities and the need for reasonable precision in the estimation of effects to inform the sample size calculation for a full-scale trial to test effectiveness.

The use of four stroke services per arm (12 in total) will provide a satisfactory indication of likely effectiveness and help us address any feasibility issues relating to the delivery of the interventions. It will also provide some degree of confirmation regarding the size of the intra-class correlation coefficient and will enable us to perform a review of the number of sites (and the number of patients needed per site) for each arm of the trial for a full-scale trial. It will also provide some information on stroke service-level factors which may help explain the variability in outcome between stroke services in each arm, thus helping reduce the intra-class correlation coefficient and hence achieve efficiency in terms of the number of stroke services required for a full-scale trial.

Twelve stroke services will admit around 4800 patients per year, of whom we expect around 20% will meet the trial inclusion criteria and consent to participate. To achieve better balance in the number of participants recruited per Trust, we will recruit for 12 months in services which admit 300 or less patients per year and for 9 months in Trusts which admit more than 300 patients per year; we expect that this will enable us to recruit 780 patients across the 12 services.

### Data analysis

#### Patient baseline data

Baseline characteristics will be summarised using means (with standard deviations), or median (inter-quartile range) if quantitative (continuous or count) as appropriate, or frequency (percentage) if dichotomous or categorical. These will be summarised both within intervention groups and within clusters (within intervention groups). All outcome data will be summarised in a similar manner.

#### Outcomes

The primary analysis set will be defined as the intention-to-treat population. All stroke services randomised will be retained in the trial. Outcome data will be collected from all consented patients whenever possible, whatever their level of subsequent engagement with the allocated intervention programme. If there is more than 10% loss to follow-up overall or moderately differential loss to follow-up across stroke services, a secondary per-protocol analysis will also be considered. The decision as to whether a per-protocol analysis will be informative will be made by the trial statistician in conjunction with other members of the Trial Management Group; this decision will be made without reference to the recorded values of the outcome data.

To account for the cluster randomisation, we shall use mixed effects modelling for continuous, ordinal and dichotomous outcomes to compare the two groups on primary and secondary outcome data. Baseline measures of the outcomes variables (where appropriate), stroke classification, type of incontinence and the other prognostic patient-level information (from the Edinburgh case-mix adjuster) will be included as individual-level covariates in the models for outcome data.

Missing outcome data will be imputed according to the particular outcome. For the primary analysis, dichotomous and ordinal outcomes for those who withdraw, die or are otherwise lost to follow-up will be imputed using a worst-case scenario (e.g. for the primary outcome variable, all those for whom incontinence status is not recorded at 6-weeks post-stroke will be assumed to be incontinent). For continuous outcomes, the primary analysis will use a non-parametric multiple imputation approach [66].

The effect of stroke service-level factors will also be explored in the modelling; this will enable appropriate stratification to be used in the future larger scale trial, if desired, and to potentially reduce the size of the intra-stroke service correlation coefficient by reducing the unexplained component of the variability between stroke services. This analysis will be used to confirm the sample size necessary for the future trial and to provide estimates (including 95% confidence intervals) of the effectiveness of each intervention relative to usual care.

Various sensitivity analyses will be performed. These will assess: the robustness of assumptions inherent in the analyses (including the use of alternative analytical approaches given the small number of clusters and of alternative approaches to imputation of missing outcome data); the effect of excluding patients subsequently found **not **to have had a stroke from analyses and the impact on the estimate of effectiveness of including patients with pre-stroke incontinence.

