Theories underpinning organisational influence include those of learning organisations (with characteristics encompassing hierarchical structure, information systems, human resource practices, organisational culture and leadership [24]) and knowledge management (how organisational mechanisms affect knowledge uptake and use [25-27]). Successful implementation of an intervention to improve the management of post-stroke urinary incontinence is likely to be mediated not only by individual members of staff and availability of evidence-based guidance, but also by the complexity of the intervention as well as the interplay of patient, social and organisational factors [28,29]. Careful attention needs to be paid to the specific barriers to change in any given setting, identified through 'diagnostic analysis' [30] at levels that may include the individual, groups or teams, organisations and the wider healthcare system [31]. Strategies then need to be 'tailored' to overcome barriers identified [32].

We therefore plan to evaluate whether supported implementation, through targeted organisational development aimed at 'normalising' the intervention [33-35], is more effective than introduction of the intervention alone, as well as evaluating both in comparison to usual care.

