### Design

A three arm, parallel, open, exploratory, pragmatic, cluster-randomised controlled trial of a systematic voiding programme (including bladder training and pelvic floor muscle training for patients who are cognitively able and prompted voiding for patients with cognitive impairments), with or without supported implementation, for the management of urinary incontinence after stroke in secondary care.

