### Centre randomisation

#### Sequence generation

Stroke services will be placed into four strata based, in order of priority, on (i) whether they have separate or combined acute and rehabilitation units (ii) their average performance on the 'nine key indicators of stroke care' in the National Sentinel Stroke Audit Phase II (clinical audit) [7] (iii) the number of stroke patients admitted per year. Services will be randomly allocated to intervention (n = 4), intervention plus supported implementation (n = 4) and usual care (n = 4) groups by the Clinical Trials Unit at Newcastle University. After allocating hospitals to the strata, the randomisation schedule will be generated using block randomisation (block length of 3) to allocate one site to each arm within every stratum. The software package STATA (version 9) will be used.

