#### Intervention fidelity data

For the intervention groups, fidelity measures will be summarised using mean (with standard deviation) or median (inter-quartile range), depending on the distributions of the percentage fidelity measures. Fidelity will be compared across intervention groups and across different conservative interventions (i.e. bladder training, prompted voiding and pelvic floor muscle training).

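### The outcome analysis refers to two groups in a three-arm trial, and names no outcome effect estimate for supported implementation against the programme alone

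*Protocol article*

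**What the plan says.** The Design section describes "A three arm, parallel, open, exploratory, pragmatic, cluster-randomised controlled trial of a systematic voiding programme", and Sequence generation allocates services to "intervention (n = 4), intervention plus supported implementation (n = 4) and usual care (n = 4) groups".

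The comparison between the two active arms is stated twice. The Objectives include to "conduct a preliminary evaluation of supported implementation compared with implementation alone". The end of the Background words it as a question of effectiveness: whether supported implementation "is more effective than introduction of the intervention alone, as well as evaluating both in comparison to usual care".

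Under Data analysis, Outcomes, mixed effects models are to be used "to compare the two groups on primary and secondary outcome data". The phrase is not defined there or elsewhere. The last paragraph of the same section says the analysis will serve "to provide estimates (including 95% confidence intervals) of the effectiveness of each intervention relative to usual care". The sensitivity analyses that follow add no comparison of the active arms. Under Intervention fidelity data, "Fidelity will be compared across intervention groups and across different conservative interventions".

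**The concern.** A three-arm trial has three pairs of arms. The sentence that governs the primary and secondary outcome models counts two groups, and the sentence that lists the effects to be reported leaves out the one pair that isolates supported implementation. The facilitation package is the only planned difference between the active arms, so that pair is what shows whether it adds anything.

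If the contrast is not reported, readers will set the two results against usual care side by side and judge the difference by eye. That gives no valid interval, because both results share the same usual-care services. The pilot is also meant to inform the size and arms of a full-scale trial, and the decision to carry the supported arm forward rests partly on this contrast. An analysis plan written faithfully from this section would carry the gap forward.

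**Working it through.** The plan gives no figure for this contrast and no power calculation, so the check is mainly of the text.

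**Step 1: contrasts asked for against contrasts promised.** Three arms give 3 × 2 / 2 = 3 pairs.

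| Contrast | Asked for in | Effect estimate with 95% CI named in Data analysis, Outcomes |
|---|---|---|
| Programme vs usual care | Background | Yes |
| Programme plus support vs usual care | Background | Yes |
| Programme plus support vs programme alone | Background and Objectives | No |

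**Step 2: possible meanings of the two groups.**
- *The two active arms.* This would cover the objective, but the model sentence would then leave out usual care and disagree with the estimates sentence in the same section.
- *Each active arm in turn against usual care.* This agrees with the estimates sentence, but leaves the objective without an outcome estimate.
- *All active services against usual care.* This disagrees with the promise of separate estimates, "of the effectiveness of each intervention relative to usual care".

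Each reading leaves something to correct.

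**Step 3: what else bears on the question.** Fidelity is compared between the active arms. The Patient baseline data section says outcome data will be summarised within intervention groups. Interviews are planned in every arm. These are process, descriptive and qualitative results. None is an estimated effect on the primary or secondary outcomes.

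**Step 4: can the missing contrast be recovered from the two named ones?** Let S, P and U be the arm means (supported, programme, usual care). Assume they are independent, each with variance v, which is reasonable with four services per arm.
- Var(S − U) = 2v and Var(P − U) = 2v.
- Treating these two as independent gives 2v + 2v = 4v for their difference.
- The correct value is Var(S − P) = 2v, because U cancels.

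A reader who combines the two published intervals as if independent gets a standard error √(4v / 2v) = √2 ≈ 1.41 times too large. The contrast has to come from the model itself.

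**Step 5: what the contrast would deliver.** Planned recruitment is 780 in 12 services: 780 / 12 = 65 per service and 4 × 65 = 260 per arm. The protocol gives neither an intra-class correlation (ICC) nor an expected six-week incontinence rate. As assumptions, take a rate p of 40% to 60% and an ICC of 0.01 to 0.10.
- Design effect = 1 + (65 − 1) × ICC: 1.64 at 0.01 and 7.40 at 0.10.
- Standard error = √(2 p (1 − p) × design effect / 260).
- At p = 0.5 and ICC 0.01: √(0.5 × 1.64 / 260) = 0.0562, so the 95% half-width is 1.96 × 0.0562 = 11.0 percentage points.
- At p = 0.5 and ICC 0.10: √(0.5 × 7.40 / 260) = 0.1193, giving 23.4 points.

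At p = 0.4 or 0.6 the two values are 10.8 and 22.9. With a t reference on 12 − 3 = 9 degrees of freedom (multiplier 2.262) the whole range becomes about 12 to 27 points. The formula is the same for all three pairs.

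**The case against.** The strongest reply is that this is a slip of wording in a condensed article. The Blinding section promises an analysis plan finalised before the statistician sees outcome data. That plan is not shown, and arm coding and contrast lists are commonly left to it. A three-arm mixed model gives the third contrast from the same fit. The objective asks only for a preliminary evaluation, which fidelity and interviews partly provide, and fidelity is close to what supported implementation is meant to change. With half-widths of 11 points or more on the assumptions above, the contrast could inform little beyond planning.

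Much of this stands, and it sets the weight of the point. It does not remove it. The article does not merely stay silent: it states a number of groups that does not fit the design, and it lists the effects to be reported in a way that omits a declared question.

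Three stronger inferences are tempting, and the document does not support them:
- *That the active arms may be pooled.* The promise of a separate estimate for each intervention rules out a pooled-only analysis.
- *That separate two-arm models will be fitted, with wider intervals because each uses only eight services.* No section says so, the plan retains all randomised services, and it fixes no degrees-of-freedom method.
- *That the supported arm goes without an estimate.* It gets one, with an interval, against usual care. What is unnamed is a single contrast, not an arm.

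**Conclusion.** The point holds in a limited form. The outcome analysis miscounts the groups, and one of the trial's three pairwise contrasts, which answers a stated objective, has no named effect estimate on the primary or secondary outcomes. Fidelity, descriptive summaries and qualitative work address the question only in part.

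The conclusion rests on the text alone. The precision figures illustrate that the contrast is about as informative as the two already promised, and they depend on the assumed rates and ICCs. It cannot be said from this document that the contrast will never be estimated, since an analysis plan not shown may name it. This is an easily repaired specification error in an exploratory pilot. It should be corrected before analysis, but it does not threaten the design or the two comparisons with usual care.

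**What to change.** In Data analysis, Outcomes, change the two groups to the three groups, and add wording such as: *For each outcome, one mixed effects model with a three-level arm factor will be fitted to all 12 services. Three contrasts will be reported with 95% confidence intervals: programme versus usual care, programme plus supported implementation versus usual care, and programme plus supported implementation versus programme alone. The last is preliminary and is for estimation only.*

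The analysis plan should carry the same list. The cost is a few sentences. No data, services or patients are added, and the target of 780 is unchanged.
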